### Recruitment {15}

All centres will perform daily screening of all ICU admissions in order to secure adequate recruitment. Recruitment of study participants will be reported to the trial sponsor and lead principal investigator via automated alert system in REDCap. Patients with SAH are critically ill and a vast majority of patients stay on the ICU or IMC for 14 days after the diagnosis; thus, loss of follow-up or other events are unlikely to interfere with the primary outcome. In addition, patients with SAH are treated in dedicated centres and—as part of their routine management—are being followed up by the neurosurgical team. Thus, we expect to gain information about their neurological outcome from a majority of our enrolled patients.

## Assignment of interventions: allocation

### Sequence generation {16a}, concealment mechanism {16b}, and implementation {16c}

REDCap will be used to allocate eligible patients in a 1:1 ratio to either the normal saline group or the lactated Ringer’s group. Randomisation will be stratified by trial site. Dedicated and trained study personnel at all sites will enrol patients and subsequently inform the team of the patients’ allocation. A box with the blinded study fluids will be given to the treating intensive care physician with the patient’s study number. Study fluid will be blinded so that no identification of the study fluid will be possible by the treatment team. The randomisation list will be held by the study’s data manager (member of the CTU of the University of Bern). All patient data will be encoded using a code for each patient included in the study. Decoding will only be possible for the primary investigator of the study. No data on patients’ identity will be presented.

## Assignment of interventions: blinding

### Who will be blinded {17a}

All study fluids are blinded by the manufacturer. All investigators, trial participants, care providers, outcome assessors, and data analysts will be blinded to patients’ allocation.

### Procedure for unblinding if needed {17b}

A list for emergency unblinding of the study will be held by research nurses of the Department of Anaesthesia, Inselspital, Bern. Access will be possible 24 h through the research nurse on call.

## Data collection and management

### Plans for assessment and collection of outcomes {18a} and plans to promote participant retention and complete follow-up {18b}, and data management {19}

Data will be obtained from the participant’s hospital files, study-specific examinations (e.g. bioimpedance results), the Insel Data Science Centre (IDSC) and national registries (mortality data) and by participant survey/interview and entered in the web-based eCRF (REDCap) by authorised trial personnel. For participants transferred from a trial ICU to a non-trial ICU, data related to the outcomes will be collected according to investigator contact with the non-trial ICU.

Long-term disability will be assessed by telephone interview or at the outpatient clinic appointment in the neurosurgical unit based on the modified the mRS, GOSE, and miniMOCA (see Figures S1–S3 in the Supplemental File for more details).

All data will be verified by regular monitoring, as well as data validity checks and automated consistency queries in the trial database. A final data quality check will be performed before the database is closed. All data changes and checks are tracked in the database.

### Confidentiality {27}

Each participant will receive a unique trial identification number. Trial investigators will receive a personal username and password to access the randomisation system and the eCRF. Each site will only have access to site-specific participant data. Data will be handled according to Swiss law. Study documentation and data are accessible to auditors/inspectors from the ethics committee and other regulatory authorities at any time. All parties involved will keep individual data strictly confidential.

### Plans for collection, laboratory evaluation, and storage of biological specimens for genetic or molecular analysis in this trial/future use {33}

No biological data will be stored.

## Statistical methods

### Statistical methods for primary and secondary outcomes {20a}

This is a parallel group study. All randomised patients receiving the study fluid will be included in the primary analysis according to a modified intention-to-treat (mITT) principle [38]. The analysis is defined as modified because patients in whom an AV-malformation is subsequently identified as the source of the haemorrhage will be excluded, since this underlying condition falls outside the intended study population; their data will contribute only to a drop-out analysis. Normal distribution of continuous variables will be tested with the Shapiro–Wilk test. Normally distributed variables are presented with mean and standard deviation. Skewed or interval and ordinal variables are presented as medians with interquartile ranges. Normally distributed interval and ordinal variables will be compared by unpaired *t*-test and skewed variables by the Wilcoxon rank sum test. Comparisons of categorical variables were performed using chi-square test or Fisher’s exact test, as appropriate [39].

Whether the use of normal saline significantly influences our primary endpoint will be assessed by a logistic regression analysis adjusted for the stratification variables (trial site) in the ITT population [40]. For the primary endpoint, deceased patients or patients who were transferred prior to reaching the primary endpoint will be counted as “no event”. A sensitivity analysis with a modified primary endpoint will be used, defined as a composite endpoint of (i) clinically relevant vasospasms during the first 14 days, (ii) ICU/IMC readmission during the 14 days (if discharged earlier) because of vasospasms, or (iii) death within 14 days.

Our secondary endpoints will be assessed by logistic (binary endpoints) as well as linear regression models (such as mRS, GOSE, and miniMOCA) adjusted for the stratification variable (trial site).

We will report absolute risk difference and relative risk ratios with 95% CIs for dichotomous secondary outcomes. For continuous secondary outcomes, we will report mean differences with 95% CIs. Missing values will be imputed with the use of the last-observation-carried-forward method for measurements made after baseline. *P* values smaller than 0.05 are considered statistically significant. Secondary outcomes will be analysed in an explorative way.

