### Who will take informed consent? {26a}

The process leading to informed consent will be in compliance with applicable regulations and national laws. The informed consent procedure will be as follows: independent physician signature will be sought prior to enrolment of the patient. If the patient presents with Glasgow Coma Scale (GCS) 15, then patient consent will be reached prior to randomisation. If the patient is cognitively impaired (GCS < 15), consent of the patient’s next of kin will be sought, with deferred informed consent by the patient. The investigators will explain to each participant or next of kin the nature of the study, its purpose, the procedures involved, the expected duration, the potential risks and benefits, and any discomfort it may entail.

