### Sample size {14}

Sample size calculation was based upon our ICU’s registry data (PDMS). In 2017, 71/160 (44.38%) patients with SAH reached our predefined endpoint of clinically relevant vasospasm requiring immediate intervention. Studies evaluating other prophylactic measures against vasospasm, such as clazosentan, magnesium, or cilostazol, have reported relative risk reductions ranging from approximately 10% to 50% [37]. Based on these findings, we considered the expected effect of the fluid intervention to lie in the mid-range, corresponding to about a 30% relative risk reduction. With an assumed baseline event rate of 45%, this translates into an absolute risk reduction of approximately 15 percentage points. The sample size was calculated with the Power and Sample Size Calculator provided by the Statistical Institute of the Medical University of Vienna (http://statistics.msi.meduniwien.ac.at) and cross checked on http://powerandsamplesize.com. The calculation revealed that at least 160 patients per group are required to detect a reduction of 15% of clinically relevant vasospasms with an alpha-error of 0.05, a power of 80%, and a drop-out rate of 15%.

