### Methods in analysis to handle protocol non-adherence and any statistical methods to handle missing data {20c}

A logistic regression analysis in the per protocol population adjusted for the stratification variable (trial site) is planned. Missing data is handled by the last observation carried forward method. In case the number of drop-outs exceeds the expected rate of 15%, the excess drop-outs will be replaced by recruitment of new subjects.

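### The primary model adjusts for trial site only and names no risk-scale effect measure; adding admission GCS and a marginal risk difference is a low-cost improvement with a modest, uncertain power gain

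*Protocol article*

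**What the plan says.** Under Statistical methods {20a}, the effect on the primary endpoint will be "assessed by a logistic regression analysis adjusted for the stratification variables (trial site"). Site is also the only stratification factor (sequence generation {16a}), and the per-protocol model in {20c} and the secondary models in {20a} use the same adjustment. No model names a patient-level baseline covariate.

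Eligibility {10} covers all adults with non-traumatic SAH admitted to intensive or intermediate care, with few exclusions. Section {26a} makes the consent route depend on GCS: "If the patient presents with Glasgow Coma Scale (GCS) 15, then patient consent will be reached prior to randomisation". Patients below 15 go through next of kin. GCS must therefore be known for every patient before enrolment, at least as 15 versus below 15.

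On effect measures, {20a} says: "We will report absolute risk difference and relative risk ratios with 95% CIs for dichotomous secondary outcomes". It makes no matching statement for the primary endpoint, which {12} defines as dichotomous. The sample size section {14}, by contrast, works on the risk scale: "With an assumed baseline event rate of 45"% , and "this translates into an absolute risk reduction of approximately 15 percentage points".

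**The concern.** Two features of a stated analysis could be improved at little cost.

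**Covariates.** The population runs from GCS 15 to impaired consciousness, while randomisation and model both ignore severity. If GCS predicts the endpoint, leaving it out of a logistic model loses some power, and any chance imbalance in severity between arms passes into the estimate. Efficiency matters here because 160 per group is about what the calculation needs before any drop-out is allowed for, although {14} says the allowance is included.

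**Effect scale.** The trial is sized on a risk difference, but the one analysis stated for the primary endpoint is a logistic regression, whose direct output is an odds ratio. With an endpoint this common, the odds ratio lies well away from the risk ratio, and a reader who takes one for the other will overstate the effect.

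**Working it through.** **1. The plan's own figure.** Inputs from {14}: 45% versus 30%, "with an alpha-error of 0.05, a power of 80%, and a drop-out rate of 15"%. Sidedness is not stated, so two-sided is assumed.

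- Unpooled: n = (1.960 + 0.842)² × (0.45×0.55 + 0.30×0.70) / 0.15² = 7.849 × 0.4575 / 0.0225 = 159.6, so 160 per arm.
- Pooled variance under the null gives 163 per arm.
- Allowing for 15% drop-out: 160/0.85 gives 189, and 163/0.85 gives 192.

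The stated 160 thus matches the requirement with no drop-out allowance. If 15% are lost, 160 × 0.85 = 136 per arm are analysed. Power (pooled formula) is 79.4% at 160 and 72.7% at 136. Section {20c} replaces only drop-outs above 15%.

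**2. What GCS could add.** The protocol gives neither the GCS distribution nor its association with the endpoint, so both are assumed: 50% or 65% of patients below 15, and a conditional odds ratio for the endpoint from 1 to 5. Arm risks were held at 45% and 30%, with three sites in assumed shares of 50/30/20%. There were 4,000 simulated trials per scenario, using a two-sided Wald test. Each trial was analysed with arm and site, then with arm, site and GCS (below 15 versus 15).

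Power, site only → with GCS:

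| GCS odds ratio | 136/arm, 50% below 15 | 136/arm, 65% below 15 | 160/arm, 50% below 15 | 160/arm, 65% below 15 |
|---|---|---|---|---|
| 1 | 72.7 → 72.4 | 71.9 → 71.6 | 78.1 → 77.9 | 78.6 → 78.7 |
| 1.5 | 72.6 → 73.0 | 72.0 → 72.4 | 80.2 → 80.4 | 78.6 → 78.7 |
| 2 | 73.4 → 74.9 | 71.6 → 73.0 | 80.1 → 81.2 | 79.7 → 80.8 |
| 3 | 73.0 → 75.6 | 72.3 → 74.5 | 78.0 → 80.8 | 78.7 → 81.1 |
| 5 | 73.3 → 79.9 | 73.0 → 77.4 | 79.6 → 84.9 | 81.1 → 84.0 |

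The simulation error of each power is √(0.73 × 0.27 / 4000), about 0.7 points. At 136 per arm the gain is nil at odds ratio 1, under 1 point at 1.5, about 1.5 at 2, 2 to 3 at 3, and 4 to 7 at 5.

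To judge how strong an odds ratio of 5 is: with half the patients below 15, it means control risks of about 26% at GCS 15 and 64% below 15. These average 45%, and (0.64/0.36)/(0.26/0.74) is about 5.

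**3. Effect scale at the design assumptions.**

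- Risk difference: 45% − 30% = 15 points.
- Risk ratio: 0.30/0.45 = 0.67, a 33% relative reduction.
- Odds ratio: (0.30/0.70)/(0.45/0.55) = 0.429/0.818 = 0.52.

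Read as a risk ratio, 0.52 would suggest a 48% reduction. This step needs no assumption beyond the plan's own rates.

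**The case against.** **Site-only adjustment is not an error.** It matches the stratified design and the test is valid; a richer model can be seen as preference. This stands as to validity. The model is nonetheless stated and not left open, so proposing a better one before unblinding is fair comment.

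**The power loss is unproven.** Nothing in the protocol says that GCS predicts vasospasm requiring intervention. Counting patients who die before the endpoint as having no event, as {20a} does, could weaken any such association by placing some of the sickest patients in the no-event group. This stands, which is why the gain is given only as a conditional range.

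**The 136-per-arm base may be pessimistic.** Deaths and transfers stay in the primary analysis, and {15} expects little loss for the primary outcome. This stands too. At 160 analysed the gain is about 0 to 1 point for odds ratios up to 2.

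**A reader might infer that adjustment wins back most of the power lost to the missing drop-out allowance.** A strong continuous severity score could do so: simulated at 136 per arm with a normally distributed score of AUC 0.74 to 0.77, adjusted power is about 79 to 82%. With AUC near 0.64, however, the gain is only about 1 point, and the protocol does not show that any recorded variable reaches the upper values. The full GCS may carry more information than the two-way split, but how much is unknown. The SOFA and acute physiology scores appear only in the abbreviation list, and no CT haemorrhage-volume grade is mentioned, so none of these can be relied on as a recorded baseline covariate.

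**The effect measure may be settled in the SAP.** Section {20a} does not say that the primary will be reported only as an odds ratio, and crude risks can be derived from arm counts. That is fair. But it expressly limits its promise of risk measures to secondary outcomes, so the text as written should be extended.

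**Conclusion.** The point holds as a recommendation for improvement, not as a finding of invalidity. The primary model omits a baseline variable that the consent procedure obtains for every patient. Including it would protect against chance imbalance in severity and may add power: nothing if GCS does not predict the endpoint, about 1.5 to 3 points at odds ratios of 2 to 3, and 4 to 7 points only at an odds ratio of 5. These figures rest on an assumed association, assumed GCS shares, a two-way split and 136 analysed per arm. Only the most favourable of these scenarios (odds ratio 5, half the patients below 15) reaches about 80%. Adjustment is therefore no substitute for correcting the drop-out arithmetic, where the pooled formula calls for 192 per arm (384 in total) if the 15% loss occurs.

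The effect-scale part rests on the text alone. The primary is sized on 15 percentage points, risk measures are promised for secondary outcomes only, and at the design rates the odds ratio (0.52) and the risk ratio (0.67) differ materially.

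**What to change.** Before unblinding, in the SAP and the next protocol version:

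- Specify the primary logistic model with arm, site and admission GCS as assessed before randomisation. Fix its form in advance: the full score if it is recorded, otherwise 15 versus below 15.
- Report for the primary endpoint a standardised (marginal) risk difference and risk ratio with 95% CIs from that model, beside the odds ratio.
- Keep the site-only model as a supportive analysis.
- Correct the drop-out allowance in {14} as a separate matter.

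The first three are changes of wording and need no new assessments if GCS is entered in the eCRF. That should be confirmed, since the protocol shows only that GCS is assessed. There is no interim analysis and the analysts are blinded, so the change can still be made without knowledge of results; after unblinding, the choice of covariate would be open to challenge. The one small downside is that the adjusted odds ratio is conditional on GCS and not directly comparable with the site-only one, which the marginal measures address. If GCS turns out not to be prognostic, the cost in power is negligible (changes of 0.4 points or less at odds ratio 1, within simulation error).

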### Outcomes {12}

#### Primary endpoint

The primary endpoint is the occurrence of clinically relevant vasospasm requiring immediate intervention as mentioned above during ICU/IMC stay. Clinically relevant vasospasm will be defined as any vasospasm requiring medical intervention (conservative or endovascular). The outcome will be analysed as a dichotomous variable.

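### The primary analysis scores every patient transferred before the endpoint as a non-event, although outcome data from a receiving ICU are to be collected and can meet the endpoint as defined

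*Protocol article*

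**What the plan says.** The primary endpoint is the "occurrence of clinically relevant vasospasm requiring immediate intervention as mentioned above during ICU/IMC stay", analysed as a yes/no variable (Outcomes {12}, Primary endpoint). The window is the stay in intensive or intermediate care. Nothing limits it to a participating unit.

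Section {20a} states that the treatment effect on this endpoint is "assessed by a logistic regression analysis adjusted for the stratification variables (trial site) in the ITT population". It then fixes the scoring rule: "deceased patients or patients who were transferred prior to reaching the primary endpoint will be counted as" having had no event.

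The data collection section ({18a}, {18b}, {19}) states: "For participants transferred from a trial ICU to a non-trial ICU, data related to the outcomes will be collected according to investigator contact" with that unit.

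Section {20a} also plans one alternative: "A sensitivity analysis with a modified primary endpoint will be used, defined as a composite endpoint of" three components. These are vasospasm in the first 14 days, readmission to ICU/IMC for vasospasm within that period after earlier discharge, and "death within 14 days". Mortality in the ICU, in hospital and at 90 days is reported separately among the secondary endpoints.

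**The concern.** The scoring rule in {20a} carries no condition. It does not say that a transferred patient is a non-event only if nothing further is known. Yet the protocol arranges to learn what happened to patients who go on to another ICU. For them, an observed endpoint would be replaced by its opposite in the analysis that decides the trial.

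Two things are at stake. Real events lost in both arms shrink the absolute difference and cost power. If losses differ between arms, the arm that loses more events looks better.

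The same sentence treats death before vasospasm as a non-event. This is a different matter, because no vasospasm was observed in those patients. It has the same arithmetic consequence, however: an arm with more early deaths has fewer patients left in whom vasospasm can be recorded.

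**Working it through.** **1. The sections side by side, for one patient.** A patient moves from a trial ICU to a non-trial ICU without vasospasm so far, and is treated there for clinically relevant vasospasm.

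- Endpoint definition: event, since it occurs during an ICU stay.
- Data collection section: the information is to be obtained from the receiving unit.
- Scoring rule in {20a}: no event.
- Composite sensitivity analysis: event if within 14 days, because that component is not tied to a unit; not counted if later.

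The first three cannot all be followed. For a patient who leaves intensive or intermediate care for a ward, there is no clash: the endpoint window has closed, and a non-event is consistent with it.

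**2. The plan's own design figures.** Inputs from Sample size {14}: 45% versus 30% (15 points absolute), alpha 0.05, 80% power, 160 per group. Two-sided, unpooled variance:

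n = (0.45×0.55 + 0.30×0.70) × (1.960 + 0.842)² / 0.15² = 0.4575 × 7.85 / 0.0225 ≈ 160 per group.

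This matches the stated figure before any allowance for drop-out. The drop-out allowance is a separate question and does not bear on this point. Patients scored as non-events stay in the analysis, so 160 per group is the right base here. Power at 160 per group, using the pooled variance under the null, is 79.4%.

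**3. Illustration: equal loss of events.** Let m be the share of would-be events lost through the rule, the same in both arms. The protocol does not give m; 5% to 15% is assumed. Recorded rate = p × (1 − m).

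| m | Ringer's lactate | Saline | Difference | Power, 160 per group |
|---|---|---|---|---|
| 0% | 45.0% | 30.0% | 15.0 points | 79.4% |
| 5% | 42.8% | 28.5% | 14.3 points | 76.1% |
| 10% | 40.5% | 27.0% | 13.5 points | 72.6% |
| 15% | 38.3% | 25.5% | 12.8 points | 68.9% |

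The risk ratio does not change. The odds ratio moves little: from (0.30/0.70)/(0.45/0.55) = 0.524 to (0.27/0.73)/(0.405/0.595) = 0.543 at m = 10%.

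**4. Illustration: unequal early death.** Assume no true effect on vasospasm, with a 45% risk in both arms among patients still at risk. Let d be the share dying before vasospasm. Recorded rate = 0.45 × (1 − d), so the spurious difference is 0.45 × (difference in d).

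- 10% versus 15%: 0.45 × 5 = 2.25 points; the nominal 5% test rejects in 7.0% of trials at 160 per group.
- 10% versus 20%: 0.45 × 10 = 4.5 points; it rejects in 13.1%.

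Both differences favour the arm with more early deaths. Neither value of d comes from the protocol.

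**The case against.** The strongest reply has four parts.

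**Scope.** {20a} does not define transfer. If it mainly means leaving ICU/IMC, the rule only applies the endpoint window. Data from non-trial ICUs also serve mortality, length of stay and the composite, so collecting them need not imply use in the primary analysis. This stands in part. It confines the clash to patients who go to another ICU or IMC, but it does not remove it, because the endpoint definition includes those stays and the scoring rule makes no exception.

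**Existing safeguard.** The composite counts death within 14 days and can take in vasospasm after transfer within 14 days. Recruitment {15} adds that the vast majority of patients stay 14 days. This is real mitigation. It leaves the primary result unchanged, however, and since the composite alters the window, adds readmission and adds death together, a discrepancy could not be traced to one rule.

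**Power.** A reader might infer that power drops to about 62%. That figure assumes 15% of events lost and 136 per group (160 × 0.85). The documents do not support it: patients scored as non-events are not drop-outs, and no transfer share is given. In addition, the 71/160 (44.38%) registry rate may already count early deaths and transfers as non-events, in which case part of the dilution is already in the 45%.

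**Death.** A reader might also infer that the death rule invalidates the primary analysis, given cited mortality of up to 50%. That figure has no time frame and is not mortality before vasospasm. Counting only observed vasospasm is a disclosed choice on which statisticians differ, and mortality is reported alongside it. If early deaths were more frequent on Ringer's lactate, as the protocol's rationale would suggest, the rule would work against the saline hypothesis.

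**Conclusion.** The inconsistency is in the text and needs no assumption: a vasospasm documented at a receiving ICU satisfies the endpoint definition and is scored as absent in the primary analysis. It applies to transfers to another ICU or IMC, not to every transfer. Its frequency is not stated, so the claim that known events will be erased holds only where a receiving unit reports one. The power figures are illustrations under assumed losses, and upper values if the registry rate already contains such losses.

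The death rule is not an error. Because unequal early death would favour the arm with more deaths, it merits one isolating sensitivity analysis and by-arm counts, and no more. Overall this is a specific correction to a stated rule, worth making before the data are analysed. It is not a defect that undermines the trial.

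**What to change.** Replace the transfer part of the rule in {20a} with wording to this effect: for patients transferred to another ICU or IMC, the primary outcome is the one obtained from the receiving unit; only if it cannot be obtained is it treated as missing, and the result is then shown with all such patients counted as events and with all counted as non-events. Exempt this outcome from the general last-observation-carried-forward rule, which would carry forward the absence of vasospasm at transfer and so restore the non-event. Discharge to a ward may remain a non-event under the stated window, provided that transfer is defined.

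Add two low-cost items: a table by arm of deaths and transfers before vasospasm, and one sensitivity analysis that keeps the primary window and changes only the death rule, counting death before vasospasm as an event.

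The cost is a sentence or two, a short table, the bounds and one extra model. The data are already to be collected. With blinded analysts and no planned interim analysis, the change can be made without knowledge of results by arm.
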